**Figure 3 figure3:**
[figure not shown]
Based on the results of the previous data, we speculated that the brain regions that may be activated include the temporal lobe, the frontal lobe, and the parietal lobe.

##### Gut Microbiota

For stool specimen collection, we will collect approximately 5 g of fecal specimen per research participant within 1 week of enrollment. The sample will be placed in a 40-mL sterile fecal drying box, immediately sealed, and numbered, before transporting it in a heat preservation box with an ice pack within 1 h of collection and storing it in a refrigerator at –80°C. The samples will be sent for inspection after all of the specimens have been collected. Approximately 200-300 mg of stool specimens will be extracted using the stool FastDNA kit (MP Bio), and the 16S rRNA gene will be amplified with specific primers (16S V4: 515F-806R). All polymerase chain reactions will be performed using Phusio high-fidelity PCR Master Mix (New England Biolabs), and the library will be sequenced on the Illumina HiSeq 2500 platform. The 16S rRNA sequencing data will be analyzed using the Quantitative Insights into Microbial Ecology platform quantitative analysis (version 1.9.1; Majorbio Inc), and we will select operating taxonomic units with a similarity threshold of 97%. We will use the serial number standard corresponding to the sample with the least sequence to normalize the abundant information of operating taxonomic units. For each representative sequence, the classification information is marked according to the GreenGene database of the RDP classifier algorithm.

### Statistical Analysis

SPSS (version 25.0; SPSS Inc Chicago) will be used for statistical analysis. The baseline characteristics of patients in each group will be analyzed descriptively. All numerical data will be expressed as the average value, X̄ (SD). Quantitative data that do not fit a normal distribution will be expressed as the median (IQR). In all analyses, statistical significance will be set as a 2-tailed *P*<.05. For the primary outcome, CFS scores will be assessed using a linear mixed-effects model with time and group interaction effects. Bonferroni correction will be used to account for multiple comparisons.

For fMRI analysis, we will select the largest peak coordinate of the brain area with a difference after amplitude of low frequency fluctuations analysis, save the block where the peak coordinate is located as the mask as the region of interest, and count the difference in the functional connection density between the region of interest and the whole brain. The specific process is to make a functional connection between the seed area (amplitude of low frequency fluctuation difference brain area) and all voxels of the whole brain. Each voxel will be given a correlation value, and the normal distribution *z* scores of the 2 sets of images will be obtained using Fisher transformation, (where r is the correlation coefficient):

That is, the functional connectivity density average image. Two-sample 2-tailed *t* test will be performed between the groups, and a paired *t* test was performed within the groups. *P* values less than .05 will be taken to indicate statistical significance and the brain regions will be corrected by FWE, while XJVIEW will be used to present the results.

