### Sample Size Calculation

According to our published paper, the efficacy of the PLWNT group is assumed to be better than that of the CBT group. Referring to our previously published study [47] on the efficacy of CFS with respect to the Multidimensional Fatigue Inventory 20 (MFI-20) scale, the final difference between the 2 groups in terms of MFI-20 average scores was 1.634 and the SD was 3.238. The Bonferroni conservative comparison method was used, and the sample size of this trial was calculated using the following formula:

Considering the allowable 20% dropout rate, the sample size of each group was set at 104. Therefore, this randomized controlled trial needed to recruit 208 participants.

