#### Primary Outcome

The MFI-20 is widely used for the measurement of mental and physical fatigue in patients with CFS [51]. It comprises 20 items, with 5 dimensions, that is, general fatigue, physical fatigue, mental fatigue, reduced activity, and reduced motivation. The total possible score is 100 points, where the higher the score, the more severe the fatigue. These will be measured at weeks 0, 4, 8, and 12.

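### The trial is sized on one final MFI-20 difference, but the primary analysis is a time-by-group interaction with no primary visit or deciding contrast named

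*Protocol article*

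**What the plan says.** The protocol article touches the primary comparison in four places.

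- **Sample Size Calculation.** The input is one quantity: "the final difference between the 2 groups in terms of MFI-20 average scores was 1.634 and the SD was 3.238". The section also says "The Bonferroni conservative comparison method was used", without giving a number of comparisons in the text available, and then "Considering the allowable 20% dropout rate, the sample size of each group was set at 104".
- **Primary Outcome.** For the MFI-20: "These will be measured at weeks 0, 4, 8, and 12". None of these visits is singled out.
- **Statistical Analysis.** "For the primary outcome, CFS scores will be assessed using a linear mixed-effects model with time and group interaction effects", followed by "Bonferroni correction will be used to account for multiple comparisons". The significance level is a two-tailed 0.05 in all analyses. The section does not say which visits enter the model, which contrast decides the trial, or which comparisons are corrected.
- **Table 1 and Follow-Up.** MFI-20 is also collected at T20, 8 weeks after treatment ends, to judge long-term efficacy.

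**The concern.** The sizing and the analysis do not aim at the same quantity. The sample size asks whether the arms differ at the end. A time-by-group interaction asks whether the difference between arms changes over the visits.

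With time as a category, that interaction has several degrees of freedom and no direction. It can be significant because of an early, passing difference, or because PLWNT does worse. The stated objective is directional: a positive effect compared with CBT. The article does not say whether the interaction, a visit-specific contrast or some Bonferroni-corrected set of contrasts decides success. A positive primary result could therefore come without the effect that the trial was sized to detect, and readers could dispute which result counts.

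**Working it through.** **Inputs.** Difference 1.634, SD 3.238, 20% dropout and 104 per group (Sample Size Calculation); 1:1 allocation (Abstract); two-sided 0.05 (Statistical Analysis); visits 0, 4, 8, 12 (Primary Outcome). Power is not in the available text because the formula was not reproduced, so it is varied here. The within-patient correlation rho, the covariance structure and the pattern of the effect over time are assumptions.

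**1. Reproduce 104 per group.** The standardised difference is 1.634/3.238 = 0.505, and its square is 0.2547. With n = 2(z_alpha + z_beta)²/0.2547:

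- alpha 0.05, 90% power: 2(1.960 + 1.282)²/0.2547 = 82.5, so 83;
- alpha 0.05/3, 80% power: 2(2.394 + 0.842)²/0.2547 = 82.2, so 83.

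Both give 83/0.8 = 103.75, so 104. The stated size reproduces exactly, but it cannot tell these two designs apart.

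**2. Can the interaction succeed without a week-12 difference?** Take categorical time, four visits (0, 4, 8, 12), compound symmetry and 83 evaluable per arm. The interaction test has 3 df and noncentrality

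lambda = (n/2) × Σ(e_j − ē)² / [SD²(1 − rho)],

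where e_j is the between-arm difference at visit j and ē is the mean of the e_j. Here (83/2) × 0.2547 = 10.57. If the arms differ by 1.634 at week 4 only, Σ(e_j − ē)² = 0.75 × 1.634², so lambda = 0.75 × 10.57/(1 − rho):

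- rho 0.3: lambda = 11.3, probability of significance 82%;
- rho 0.5: lambda = 15.9, probability of significance 93%.

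A test of the week-12 contrast alone would reject 5% of the time in this scenario.

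**3. Power of one week-12 contrast.** With 83 per arm, the expected z is √10.57 = 3.251.

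- Unadjusted, alpha 0.05: Φ(3.251 − 1.960) = 90.2%.
- Unadjusted, alpha 0.05/3: Φ(3.251 − 2.394) = 80.4%.
- Baseline-adjusted, alpha 0.05, with SD multiplied by √(1 − rho²): 92.6% (rho 0.3), 96.4% (rho 0.5), 99.5% (rho 0.7). This requires 3.238 to be the SD of the final score, which the text does not say.

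**4. Compare with the interaction test when there is a true week-12 effect of 1.634.**

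| Scenario | Interaction, 3 df | Baseline-adjusted week 12 |
|---|---|---|
| Compound symmetry, linear build-up, rho 0.3 / 0.5 / 0.7 | 67.7% / 83.1% / 97.2% | 92.6% / 96.4% / 99.5% |
| Compound symmetry, constant from week 4, rho 0.3 / 0.5 / 0.7 | 81.6% / 93.2% / 99.5% | 92.6% / 96.4% / 99.5% |
| AR(1), constant from week 4, rho 0.7 | 96.2% | 93.3% |

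The single contrast does better in most scenarios tried, ties in one and loses in the last row.

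**The case against.** The strongest reply is that the two sections do not disagree about multiplicity. A reader might infer that the analysis carries a Bonferroni penalty for which the sample size made no allowance, or that 208 is too few. The documents do not support either. The sizing text names Bonferroni too, and 104 per group is what three corrected comparisons at 80% power require; three post-baseline visits would fit. On that reading 80% is the design power, not a loss. The formula is missing from the available text and may have stated the number of comparisons. This part of the objection stands.

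Second, several features are inferred. The analysis section does not say that time is categorical, that week 0 is an outcome rather than a covariate, that the test is omnibus, or that alpha is split across visits. This also stands: the 82% and 93% belong to one reading, though it is the natural one.

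Third, a reader might fear a primary win driven by week 20. The Primary Outcome section lists weeks 0 to 12 only, and Follow-Up assigns the later assessment to long-term efficacy, so that fear is not well founded.

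Fourth, the claim of higher power depends on the correlation, the covariance structure, the effect pattern and what the SD measures. That is correct, and one AR(1) case goes the other way.

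Fifth, baseline covariates and contrasts are details that an article may leave to the analysis plan, and a single omnibus test or a fully corrected family would control type I error. Both are fair. But the article does set out the primary outcome, its visits, the model and the correction, and together they do not fix one deciding test. The problem is what a significant result would mean, not inflated error.

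**Conclusion.** The point holds in a limited form. The sizing targets one final difference, the primary analysis is a time-by-group interaction with an undefined Bonferroni family, and no primary visit or deciding contrast is named. Under categorical time, week 0 as an outcome and compound symmetry, a week-4-only difference of 1.634 would make the interaction significant with probability about 82% (rho 0.3) or 93% (rho 0.5).

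An error in the sample size is not shown, nor is a multiplicity penalty left out of it. If three corrected comparisons were intended, testing one unadjusted contrast instead raises power from 80% to 90% at the same size. Baseline adjustment takes it to about 93% or 96% at those two correlations, provided 3.238 is the SD of the final score. The gain over the interaction test is usual, not guaranteed.

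**What to change.** - Name the between-arm difference in MFI-20 total at week 12 as the single primary contrast.
- Estimate it from the planned mixed model fitted to weeks 4, 8 and 12, with group, visit and group-by-visit terms and the T0 MFI-20 as a covariate. Test it once at two-sided 5%.
- Make weeks 4, 8 and 20 secondary.
- Say which comparisons Bonferroni covers in Statistical Analysis. In Sample Size Calculation, state the number of comparisons and the power, or remove the reference. Say also whether 3.238 is the SD of the final score or of change.

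The cost is wording only; every measurement is already scheduled. The Results section reports that no analysis has been performed, so the change can be made and dated before the data are examined. The one small loss is that early or non-monotone effects would no longer count toward the primary test; they would be reported as secondary results.

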**Methods:**

We will conduct a randomized, analyst-blinded, parallel-controlled trial with a 12-week intervention and 8-week follow-up. A total of 208 patients of age 20-60 years will be recruited. The patients will be randomly divided into a PLWNT Qigong exercise group (PLWNT Group) and a control group treated with cognitive behavioral therapy at a ratio of 1:1. Participants from the treatment groups will be taught by a highly qualified professor at the Shanghai University of Traditional Chinese Medicine once a week and will be supervised via web during the remaining 6 days at home, over 12 consecutive weeks. The primary outcome will be the Multidimensional Fatigue Inventory 20, while the secondary outcomes include the Pittsburgh Sleep Quality Index, Gastrointestinal Symptom Rating Scale, Hospital Anxiety and Depression Scale, functional magnetic resonance imaging, gut microbiota, and peripheral blood.

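### Bonferroni is valid but avoidably inefficient: Holm's step-down procedure gives the same familywise control and never rejects less in the Bonferroni-corrected comparisons

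*Protocol article*

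**What the plan says.** The Statistical Analysis section sets one significance rule ("In all analyses, statistical significance will be set as a 2-tailed" P<.05) and one multiplicity rule: "Bonferroni correction will be used to account for multiple comparisons". For the primary outcome, "CFS scores will be assessed using a linear mixed-effects model with time and group interaction effects". The Primary Outcome section says of the MFI-20: "These will be measured at weeks 0, 4, 8, and 12"; Table 1 adds a week-20 follow-up.

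The Sample Size Calculation section names the same method and calls it conservative: "The Bonferroni conservative comparison method was used". It does not give the number of comparisons or the power.

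The article mentions no step-down version, does not say which comparisons form the family, and gives no reason for preferring Bonferroni, such as a wish for simultaneous intervals. The fMRI maps are handled separately, by an FWE correction.

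**The concern.** Bonferroni tests every member of a family of m at 0.05/m, however many of the others have already been rejected. Holm uses 0.05/m only for the smallest P value, then 0.05/(m-1) for the next, and so on up to 0.05, stopping at the first failure. Both control the familywise error strongly at 5% with no assumption about dependence. Each Holm threshold is at least as large as 0.05/m, so no Bonferroni rejection is lost.

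The difference shows when more than one null hypothesis is false. That is what this trial hopes for: the last paragraph of the Introduction hypothesizes benefit on fatigue, insomnia, anxiety and gastrointestinal symptoms, and the MFI-20 is measured at three post-baseline visits during the intervention. Whether the corrected comparisons turn out to be visits or scales, some real effects may be reported as not significant under Bonferroni when an equally strict procedure would have declared them.

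**Working it through.** **Inputs from the article.** The difference and SD come from Sample Size Calculation ("in terms of MFI-20 average scores was 1.634 and the SD was 3.238"), as do dropout and group size ("Considering the allowable 20% dropout rate, the sample size of each group was set at 104"). Allocation is from the Abstract ("a control group treated with cognitive behavioral therapy at a ratio of 1:1"), and the level is 0.05 two-sided.

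**Inputs assumed, because the article does not give them.** Family sizes of 2, 3 and 4; correlations between test statistics of 0, 0.5 and 0.8; and the pattern of true effects across the tests.

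**Step 1: the plan's own figure.** The standardized difference is 1.634/3.238 = 0.505. With n per group = 2(z for alpha + z for power)² / 0.505², rounded up, and then n/(1 - 0.20):

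- alpha 0.05/3, power 80%: n = 83, and 83/0.8 = 103.75, so 104.
- alpha 0.05, power 90%: n = 83, so again 104.

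The stated 104 per group is reproduced exactly either way. The article does not say which route was taken.

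**Step 2: power of one test under Bonferroni.** The expected z is 0.505 × √(83/2) = 3.25. Against a two-sided level of 0.05/m, power is 84% for m = 2, 80% for m = 3 and 77% for m = 4.

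**Step 3: Holm on the same data.** Both procedures were applied to the same simulated two-sided z tests, 300,000 runs per scenario. Ranges run over the three correlations. In the first table every test has the planned effect of 0.505.

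| Family | Power per test, Bonferroni | Power per test, Holm | All rejected, Bonferroni | All rejected, Holm |
|---|---|---|---|---|
| 2 tests | 84% | 88-89% | 71-78% | 81-85% |
| 3 tests | 80% | 86-88% | 52-69% | 72-81% |
| 4 tests | 77% | 84-87% | 36-62% | 64-78% |

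**Step 4: less favourable patterns, three tests.** With effects of 0.4, 0.7 and 1.0 times the planned one:

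| Correlation | Smallest effect, Bonferroni to Holm | Largest effect, Bonferroni to Holm |
|---|---|---|
| 0 | 13.8% to 20.6% | 80.4% to 83.0% |
| 0.5 | 13.7% to 22.7% | 80.5% to 81.7% |
| 0.8 | 13.7% to 24.3% | 80.5% to 80.8% |

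The gain is therefore about 7 to 11 points for the smallest effect and 0 to 3 for the largest. With only one real effect, power for it goes from 80.5% to 80.6% at correlation 0, and the gain is no larger at the other correlations.

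**Step 5: error control and first rejection.** With three true nulls, the familywise error was identical for the two methods: 4.9%, 4.4% and 3.5% at correlations 0, 0.5 and 0.8. With one real effect and two true nulls it was 3.3%, 3.1% and 2.7% for Bonferroni and 4.6%, 4.1% and 3.4% for Holm. Holm uses more of the allowed 5% but does not exceed it. The probability of at least one rejection was the same for both methods in every scenario, because the first step is the same test. No run had a Bonferroni rejection that Holm missed.

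**The case against.** The strongest reply is that nothing here is wrong. Bonferroni is valid and prespecified, and it fits the sample size: 104 per group is what a three-way split with 80% power gives. On that reading, 80% per test is the designed power and not a shortfall. This stands, and it makes the point one of efficiency only. A reader might infer that the trial is underpowered or that its error rate is not controlled; the article supports neither.

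The size of the gain is also open to challenge. The article gives one final difference, not one for each of weeks 4, 8 and 12, and it states no family and no correlation. Equal effects on every test flatter Holm. This stands too, so the gain has to be read as a range starting near zero.

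The scope is limited as well. A reader might infer that power is lost in every corrected analysis, or that the primary test itself suffers. The fMRI maps have their own correction, and if the time-by-group interaction is tested once as an omnibus test, neither procedure touches it. Nor can one say that real effects will be missed, only that some may be.

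Finally, Bonferroni has simple matching simultaneous confidence intervals and Holm does not. That would be a fair reason to keep it, but the article does not invoke it.

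**Conclusion.** The point holds as a cheap improvement, not as a fault in validity. For any family of two or more comparisons under the Bonferroni sentence, Holm is never worse at the same 5% and under the same absence of dependence assumptions.

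Its value depends on how many of the tested effects are real. It is material if several are, as the trial hypothesizes, and negligible if only one is. The figures rest on 83 completers per arm, the planned effect of 0.505, and assumed family sizes, correlations and effect patterns. The conclusion that Holm is never worse rests on none of these.

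**What to change.** Replace the Bonferroni sentence in Statistical Analysis with:

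*Where several comparisons are made, P values will be adjusted by the Holm step-down procedure within each family at a two-sided familywise 5% level.*

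Apply it to the comparisons that the Bonferroni sentence was meant to cover. Holm needs that list as much as Bonferroni does, so the new wording does not by itself settle which comparisons belong to a family. Leave the fMRI correction as it is.

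The cost is one sentence. Holm is simple arithmetic on unadjusted P values from the mixed model, and 104 per group need not change because the first Holm step is the Bonferroni test. The Results section says that no data analysis has yet been done, so on the article's account the change can still be made and dated before any group comparison is seen.

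The downside is the intervals: report ordinary 95% confidence intervals and note that they may not match the adjusted decisions.

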##### fMRI

fMRI data will be obtained from all participants using the 3.0-T Trio Siemens System at the Shanghai Municipal Hospital of Traditional Chinese Medicine. Thirty-two head coils will be used for scanning. In the resting state BOLD signal acquisition single excitation gradient echo-plane imaging sequence, the participants will be scanned using the following parameters: repetition time (*T*_R_)=1900 milliseconds; effective echo time (*T*_E_)=2.93 milliseconds; sagittal slices=188; thickness/skip=1.2/0.6 mm; field of view (FOV)=256×256 mm^2^; matrix=240×256 mm^2^; voxel size=1.0×1.0×1.0; phase encoding direction=A>>P; and flip angle (*F*_A_)=90°. The participants will be asked to close their eyes, rest for 10 min, and not think about anything before the scan. The participants will be instructed to not move their heads during data collection. The 2 groups of participants will be tested before and after the experiment. Based on the results of previous studies, we speculated that the brain regions that may be activated include the temporal lobe, frontal lobe, and parietal lobe, which are shown in Figure 3.

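### The fMRI analysis makes no stated use of the baseline scan, adds within-arm tests that do not compare PLWNT with CBT, and takes its connectivity seed from the same scans

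*Protocol article*

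**What the plan says.** Under Secondary Outcome, the fMRI section states "The 2 groups of participants will be tested before and after the experiment", and Table 1 places the scans at T0 and T12. The same section says that all participants are scanned.

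The fMRI paragraph under Statistical Analysis sets out two stages. The first finds a seed: "we will select the largest peak coordinate of the brain area with a difference after amplitude of low frequency fluctuations analysis". The second is to "make a functional connection between the seed area (amplitude of low frequency fluctuation difference brain area) and all voxels of the whole brain", with Fisher-transformed correlations as the measure. The resulting maps are then tested: "Two-sample 2-tailed *t* test will be performed between the groups, and a paired *t* test was performed within the groups". Results are judged at P<.05, with family-wise error (FWE) correction for brain regions. The general rule in that section is "In all analyses, statistical significance will be set as a 2-tailed *P*<.05".

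For the primary outcome the same section specifies a different kind of contrast: "CFS scores will be assessed using a linear mixed-effects model with time and group interaction effects". No such term, and no baseline covariate, is given for fMRI.

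The fMRI section also records a prior expectation: "we speculated that the brain regions that may be activated include the temporal lobe, frontal lobe, and parietal lobe". These lobes are not used to define the seed.

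**The concern.** There are three separate issues.

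1. **Baseline.** Each participant has a T0 map, but the plan does not say that the between-arm test uses it. The text does not state whether the two-sample test takes T12 maps, change maps or each time point in turn. If it takes T12 maps alone, precision already paid for is lost.

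2. **Within-arm tests.** A paired test in one arm asks whether that arm changed. It does not ask whether PLWNT changed brain function more than CBT. The plan gives these tests the same threshold as the between-arm test and does not mark them as descriptive.

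3. **Seed choice.** The region is chosen because these scans show an amplitude (ALFF) difference there, and connectivity from that region is then tested on the same scans. FWE correction accounts for searching over voxels from a given seed. It does not account for how the seed was picked.

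At stake is the mechanistic claim. The Discussion presents brain-gut findings as the objective view of efficacy, in a trial where patients know their treatment.

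**Working it through.** **Inputs.** From the protocol: 104 per arm, 20% dropout, MFI-20 difference 1.634 and SD 3.238 (Sample Size Calculation); two-sided 5% level (Statistical Analysis); scans at T0 and T12 (Table 1). Assumed, because the documents give no fMRI figures: an effect of 0.4 SD and a pre-post correlation rho of 0.3, 0.5 or 0.7.

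**The plan's own figure.** The only reproducible figure is the MFI-20 sample size. The visible text gives no power. With a two-sided 5% level and 90% power, n = 2 × (1.960 + 1.282)² × (3.238/1.634)² ≈ 2 × 10.51 × 3.927 ≈ 82.5, so 83 per arm, and 83/0.8 = 103.75, so 104. A level of 0.05/3 with 80% power gives the same 83 and 104. I therefore use 83 completers per arm.

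**Step 1: is the between-arm test valid?** Simulation under no effect (10,000 runs, 83 per arm, the three values of rho) gave these rejection rates:

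- T12-only t test: 0.050 to 0.052
- change-score t test: 0.049 to 0.051
- ANCOVA (T12 adjusted for T0): 0.051 to 0.054

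All three hold the 5% level to within simulation error.

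**Step 2: what does ignoring baseline cost?** With T12-only variance set to 1, change-score variance is 2(1 − rho) and ANCOVA variance is about 1 − rho². At rho = 0.5 these are 1.00 and 0.75, so adjustment cuts variance by 25%. Simulated power for 0.4 SD:

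| rho | T12 only | Change score | ANCOVA |
|---|---|---|---|
| 0.3 | 0.73 | 0.58 | 0.76 |
| 0.5 | 0.73 | 0.73 | 0.84 |
| 0.7 | 0.72 | 0.91 | 0.95 |

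As a check, the T12-only expected z is 0.4 × √(83/2) = 2.58, and Φ(2.58 − 1.96) ≈ 0.73. These are powers for one pre-set measure at 5%, not for a whole-brain search under FWE. The ordering of T12-only and ANCOVA follows from the variance formulas, but the levels would differ.

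**Step 3: what do the paired tests show?** Suppose both arms change equally, so there is no treatment effect, and each paired test has power p. Exactly one arm is then significant with probability 2p(1 − p), which is 0.50 at p = 0.5 and 0.32 at p = 0.8. In the simulation, with equal true changes of 0 to 0.3 SD, this happened in 9% to 49% of trials. A split result is therefore common when the arms do not differ.

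**Step 4: what does the seed choice do?** Let r be the correlation, under no effect, between the ALFF contrast and the connectivity contrast. Taking the largest of 100 independent regions and testing connectivity there at an uncorrected |z| > 1.96, the simulated rejection rate was 0.05 at r = 0, 0.08 at r = 0.2, 0.18 at r = 0.4 and 0.37 at r = 0.6. This shows direction only. The documents do not give r, the planned threshold is FWE-corrected rather than 1.96, and the contrast defining the ALFF difference (between arms or pre-post) is not stated.

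**The case against.** The strongest reply is that this is a condensed article. Which maps enter the two-sample test may be set out in a fuller document, and it could already be the change-map test. That stands: absence of baseline from the between-arm test is the natural reading, not a stated fact. The recommendation survives it, because a change-map test is still less efficient than adjustment at every rho examined.

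A reader might infer that none of the planned fMRI tests validly assesses a treatment effect. The documents do not support that. A two-sample t test of T12 or change maps is a valid randomized comparison, as Step 1 shows. Nor does the plan say that significance in one arm only will be read as a difference between arms. It lists the paired tests beside a direct between-arm test, so Step 3 describes a misreading to guard against, not a planned inference.

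A reader might also put a large false-positive rate on the connectivity test. Fixing the seed at |t| = 4 with r = 0.3 to 0.5 gives 21% to 52% at an uncorrected 1.96. Those figures ignore the FWE threshold and rest on assumed correlations. They are also conditional on an ALFF difference being found. If FWE also governs that step (the text is unclear), about 5% of trials with no effect anywhere would reach the second stage, and 0.05 × 0.52 = 0.026. ALFF and connectivity are different measures, so this is not selection and testing on one statistic.

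Finally, the Introduction frames the brain-gut aim as exploring a mechanism, and a data-derived seed is reasonable for exploration. That also stands, and is why labelling the result exploratory is an acceptable remedy.

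**Conclusion.** The point holds in a limited form. The between-arm fMRI test is valid but, as written, makes no stated use of the T0 map. If it uses T12 maps alone, baseline adjustment would cut variance by about rho². Under the assumptions above (0.4 SD, 83 per arm, rho 0.3 to 0.7) that means power of about 0.73 against 0.76 to 0.95. The paired tests do not compare PLWNT with CBT and should carry no comparative weight. The nominal error rate of the connectivity test is assured only if the ALFF and connectivity contrasts are independent. Inflation is possible, but its size cannot be derived from the documents. fMRI is one of several secondary outcomes, and the primary MFI-20 analysis has its own group-by-time model, so the primary conclusion is unaffected.

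**What to change.** - **Between-arm test.** State that it is a voxelwise comparison of T12 maps adjusted for the T0 map, with FWE correction. A two-sample test of T12 − T0 change maps is an acceptable but less efficient alternative.
- **Within-arm tests.** Report the paired tests as descriptive only.
- **Seed.** Fix it without regard to arm or treatment response, either as a priori coordinates set before unblinding or from pooled T0 scans. Coordinates must be added, because the protocol names only whole lobes. Otherwise label the connectivity result from a data-derived seed exploratory.

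The cost is a change of wording and a little more imaging analysis time. No new data are needed, and the Results section says that data analysis has not yet been performed. The downside is that a pre-set seed may miss an unexpected region, which can still be reported as exploratory.
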